#### Secondary outcome analysis

The secondary outcome of the trial will be the incidence of procedure-specific complications by the end of the follow-up period (12 months). A binary logistic regression will be used to assess the effect of intervention allocation on complications incidence in a multivariable model containing confounders described above. Alpha will be set at 0.05 and partial eta^2^ used to assess model fit. Odds ratios with 95% confidence limits will describe the strength and direction of relationships between model predictors and the probability of having a complication compared to not having one.

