### Sample size {14}

The sample size required for the primary outcome was established to provide adequate power to detect half an MCID difference (15.3/2) in the FAOS Pain score between the control flat-cut Weil and experimental wedge-cut groups, with an average estimated baseline standard deviation of 20.8. The MCID and baseline SD were derived from a previous study [15], and 0.5MCID was determined to be a clinically important effect that would influence future clinical decision-making regarding technique selection. A mixed-effects model (analysis of covariance (ANCOVA)) was selected as the most appropriate to answer the question posed, with power (*β*) at 0.9 and *α* of 0.05, with an allowance for a dropout rate of 10%. The required sample size was determined using GPower [18] to be *N* = 80 patients, with patient age at surgery, sex, body mass index, single/multiple procedures and adjunct procedures included as model covariates.

The sample size required for the secondary outcome was established to provide adequate power to detect a 15% reduction in complication incidence from a baseline of 60% incidence. The reduction in incidence was deemed to be the minimal amount of improvement that would influence future decision-making regarding technique selection in this patient population. A one-sided test within a logistic regression model was selected within GPower, with the *R*^2^ for other predictors in the model (patient age at surgery, sex, body mass index, single/multiple procedures and adjunct procedures) set to 0.1. The required sample size was determined to be *N* = 123 procedures.

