### Recruitment {15}

The principal investigator for the study performed a total of 127 Weil osteotomies in 87 patients over the 12 months preceding the study. To meet the required sample size of *N* = 80 patients with *N* = 123 procedures to assess the primary and secondary outcomes, respectively, the expected recruitment period will extend over 12 months. All prospective patients eligible for recruitment will be approached to participate in the study.

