### Assignment of interventions: allocation

#### Sequence generation {16a}

Participants will be randomly assigned to receive either a flat-cut Weil osteotomy (control, group A) or wedge-cut osteotomy (experimental, group B) procedure using a central computer-based simple randomisation system, with a 1:1 allocation without blocking. The random allocation sequence will be embedded within the clinical registry via a randomisation algorithm (Matlab 2018b, Mathworks Inc., USA). The allocation will be communicated electronically to the treating surgeon via an allocation code comprising nondescript terminology, whereby the allocation cannot be inferred from the label to other study personnel.

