### Methods for additional analyses (e.g. subgroup analyses) {20b}

Depending on the overall incidence of procedure-specific complications (assuming that the incidence is > 5% overall) a Cox regression will be employed to compare the groups for time to event (complication detected) between day 1 postoperatively to 12-month evaluation with right censoring for participants that complete the study follow-up with no complications reported. Hazard ratios with 95% confidence intervals will be used to describe the strength and direction of the relationship between intervention allocation and time to event.

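### The secondary outcome is sized in procedures, but its logistic regression names no unit and has no patient-level term, so either the intervals ignore clustering or the 123 does not apply

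*Protocol article*

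**What the plan says.** - **Randomisation** (Sequence generation {16a}): "Participants will be randomly assigned to receive either a flat-cut Weil osteotomy (control, group A) or wedge-cut osteotomy (experimental, group B) procedure". Allocation is per person, so every osteotomy of one participant has the same technique.
- **Sample size {14}**: for the secondary outcome, a one-sided test in a logistic regression is sized to detect a 15% reduction from 60% incidence, with R² of 0.1 for the other predictors. The result: "The required sample size was determined to be *N* = 123 procedures". No design effect is mentioned.
- **Recruitment {15}**: 80 patients are paired with "123 procedures to assess the primary and secondary outcomes, respectively". The caseload behind this is that the principal investigator "performed a total of 127 Weil osteotomies in 87 patients over the 12 months preceding the study".
- **Secondary outcome analysis**: "A binary logistic regression will be used to assess the effect of intervention allocation on complications incidence in a multivariable model", with the confounders already listed and odds ratios with 95% confidence limits. No unit, patient effect or clustered variance is given.
- **Primary outcome analysis**: by contrast, patient ID is listed as a random factor.

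**The concern.** The trial has more procedures than patients, and all procedures of one patient share the arm, the patient and the aftercare. Their complication outcomes are therefore plausibly correlated. A logistic regression with one row per procedure and no allowance for this treats 123 rows as 123 independent observations of the treatment effect. The standard error of the treatment odds ratio is then too small, its 95% limits cover less often than stated, and a chance difference between techniques is declared too often.

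If one row per patient is intended, that problem disappears, but the stated sample size belongs to a different analysis. Under both readings the sample size section and the analysis section do not describe the same analysis. What is at stake is the protocol's complications objective, which this one model is meant to answer.

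**Working it through.** **The plan's own figure.** The 123 could not be reproduced for a two-arm factor. Taking the 15% as absolute (60% to 45%), one-sided 5%, the two-proportion formula gives 136 per arm at 80% power and 188 at 90% (power for this outcome is not stated; both values are assumed). Dividing by 1 − R² = 0.9: 272/0.9 ≈ 302 and 376/0.9 ≈ 418 procedures. Only treating the arm as a standard normal variable comes near, at about 120 for 90% power. That is a separate point. What matters here is that none of these calculations contains a design effect, so 123 presumes independent rows.

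**Inputs from the protocol.** 80 patients and 123 procedures, 123/80 = 1.54 per patient; historically 127/87 = 1.46 per patient.

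**Assumptions.** The protocol gives neither the ICC nor the spread of procedures per patient. I take ICC 0.1, 0.3 and 0.5. The simplest spread that fits the protocol's totals is 37 patients with one procedure and 43 with two: 37 + 43 = 80, and 37 + 86 = 123.

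**Design effect.** DE = 1 + (Σm²/Σm − 1) × ICC, with m the procedures per patient. Here Σm² = 37 × 1 + 43 × 4 = 209, and 209/123 = 1.70, so DE = 1 + 0.70 × ICC. Effective N is 123/DE. The true standard error is √DE times the unclustered one. Two-sided type I error is 2 × [1 − Φ(1.96/√DE)], and coverage is its complement.

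| ICC (assumed) | DE | Effective N | SE understated by | Type I error | Coverage of 95% limits | Procedures needed for the information of 123 |
|---|---|---|---|---|---|---|
| 0.1 | 1.07 | 115 | 3% | 5.8% | 94.2% | 132 |
| 0.3 | 1.21 | 102 | 10% | 7.5% | 92.5% | 149 |
| 0.5 | 1.35 | 91 | 16% | 9.2% | 90.8% | 166 |

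The SE column gives √DE − 1, and the last column gives 123 × DE.

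**Sensitivity to the spread.** Suppose 66/24/8/2% of patients have 1/2/3/4 procedures (assumed; mean 1.46, the historical ratio, so 80 × 1.46 ≈ 117 procedures). Then E[m²] = 0.66 + 0.96 + 0.72 + 0.32 = 2.66, and 2.66/1.46 − 1 = 0.82, so DE = 1 + 0.82 × ICC. At ICC 0.3, DE = 1.25 and effective N = 117/1.25 ≈ 94.

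**Simulation check, no true effect.**
- With this second spread, 60% incidence and 20,000 trials per ICC, the unclustered two-sided test rejected in 6.0%, 8.2% and 9.7%. The one-sided 5% test rejected in 5.8%, 7.2% and 8.3%.
- A separate simulation with 4,000 runs per ICC gave 5.4%, 8.0% and 9.0% unclustered, against 4.7% to 5.3% with patient-clustered errors.

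**Power by unit.** For 60% to 45%, one-sided 5% and R² = 0.1, 123 independent procedures give about 47% power. With DE 1.07, 1.21 and 1.35 this falls to about 45%, 42% and 39%. With 80 patients as the unit, and assuming the same 60% and 45% held per patient, it is about 35%.

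**The case against.** The strongest reply is that the analysis is per patient. The section on the secondary analysis never mentions procedures. The statistical principles analyse participants in their randomised group and use participants as the denominator. The missing-data section speaks of patients reviewed, and non-union is identified by patient. Single versus multiple procedures is listed as a predictor, which fits one row per patient. On that reading there is no clustering and no interval is too narrow.

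This stands as far as it goes. A reader might infer that the plan definitely analyses procedures and that its limits are definitely too narrow, but the protocol does not establish that. The reply does not rescue the text, however. The sample size section sizes a logistic regression for this outcome and counts it in procedures, and the recruitment section repeats the distinction from patients. On the patient reading, the 123 is not the analysed sample.

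Three further replies:
- *The listed confounders include patient ID.* It is labelled a random factor, not a confounder, and an ordinary binary logistic regression has no random term.
- *Single/multiple procedures is adjusted for.* A fixed covariate shifts the mean risk; it does not model correlation within a patient.
- *Variance estimation belongs in a fuller plan.* That is fair for the estimator alone. Here, though, the article itself states an N and a model that do not fit together.

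A reader might also extend the concern to the additional analysis, in which "a Cox regression will be employed to compare the groups for time to event (complication detected". The protocol does not support that: the same sentence right-censors participants without complications, which reads as one time per person. Clustered errors would be needed there only if it were run per procedure.

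**Conclusion.** The point holds in conditional form. The protocol sizes the secondary outcome in procedures, randomises patients, and plans a regression that neither names its unit nor contains a patient term. Under the procedure reading, 95% limits are too narrow whenever within-patient correlation is positive: two-sided type I error is about 6%, 8% and 9-10% at ICC 0.1, 0.3 and 0.5, and effective N is about 115, 102 and 91 of 123 with one or two procedures per patient. Under the patient reading the limits are sound, but N is 80.

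Positive correlation is plausible, but its size and the spread of procedures are assumptions. With about 1.5 procedures per patient the inflation is modest, and the primary analysis is not affected. Severity: should-fix. Confidence is high that the two sections do not match, and lower on the size of the inflation.

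**What to change.** State the unit in Secondary outcome analysis and make Sample size {14} and Recruitment {15} agree with it.

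- **If the procedure:** fit the logistic model by GEE with the patient as cluster and small-sample-corrected robust standard errors. GEE gives a population-averaged odds ratio. A patient random intercept gives a patient-specific one, so the two are not interchangeable and one should be named in advance. In the sample size section, add a design effect with its assumed ICC and spread of procedures, and restate the effective sample size or power.
- **If the patient:** define the outcome as any procedure-specific complication in that patient, and restate baseline incidence, N and power on 80 patients. The 60% should be re-justified, because the risk of any complication per patient need not equal the risk per procedure.

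State the unit of the Cox analysis in the same edit.

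The cost is a few sentences and a few lines of code, with no new data. Under the procedure option the intervals become somewhat wider (about 3% to 16% on the standard error over the ICC range above). Under either option the restated power may be lower than the reader now assumes.

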### Interim analyses {21b}

No interim analysis has been planned that would lead to early termination based on the results of the study. The study will be monitored for adverse events on a continual basis and reported regularly to the investigators, and an unacceptably high incidence in either treatment group (50% greater than reported in the equivalent literature) may be reviewed by the investigators and cause the trial to be terminated.

### Methods for additional analyses (e.g. subgroup analyses) {20b}

Depending on the overall incidence of procedure-specific complications (assuming that the incidence is > 5% overall) a Cox regression will be employed to compare the groups for time to event (complication detected) between day 1 postoperatively to 12-month evaluation with right censoring for participants that complete the study follow-up with no complications reported. Hazard ratios with 95% confidence intervals will be used to describe the strength and direction of the relationship between intervention allocation and time to event.

### Methods in analysis to handle protocol non-adherence and any statistical methods to handle missing data {20c}

The nature of the dataset does not lend itself to multiple imputation in the first instance. If patients have not returned the form at follow-up, despite multiple reminders, a multiple imputation approach will be employed based on published guidelines for analysis of trial data [24]. Secondary outcomes are unlikely to have missing data due to the nature of clinical follow-up and the acute nature of procedure-specific complications (i.e. all patients are reviewed in person or by phone within the timeframe that complications would be observed). In the event that missing secondary outcomes are apparent, analyses will be performed to assess the *randomness* of the missing data and to determine whether complete case analysis is appropriate. In the event that the missing data does not conform to a random pattern, sensitivity analysis using worst-case, best-case scenarios for missing data will be constructed and reported [24].

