#### Secondary outcome measures

The secondary outcome of this trial will be the incidence of procedure-specific complications at up to 12 months postoperatively. The most commonly reported complication of the Weil osteotomy is a floating toe, with an overall occurrence of 36% [6]. A floating toe is defined as a toe that is not in contact with the floor under weight-bearing conditions [16]. It will be recorded using a weight-bearing coronal view static photograph and manually rated. Recurrence is reported in 15% of the cases, followed by transfer metatarsalgia (7%) and delayed union, non-union and malunion collectively reported in 3% of the cases [6]. Metatarsal osteotomy union will be defined using cortical continuity [17], with patients failing to show any healing (nonunion) and insufficient cortical continuity (delayed) by the 12-month review, identified in the trial data.

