#### Data integrity

All data points for the study core dataset will be retrieved electronically, so comparing to original paper records will not be necessary. Data integrity will be defined in the context of this study as completeness, consistency and validity. An error rate of < 3% will be considered acceptable across the total of fields assessed.

Patients who are otherwise lost to follow-up will be included in the analysis under an intention-to-treat framework. Where appropriate, imputation will be used to provide estimates of outcomes for patients lost to follow-up. To mitigate the effects of loss to follow-up on the analysis, the sample size factored in an estimated dropout rate of 10% to ensure adequate power for analyses requiring listwise deletion of missing data.

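### Best/worst-case analysis of missing complication data is planned only if a randomness check fails, and passing that check cannot justify omitting it

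*Protocol article*

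**What the plan says.** The rule is in the protocol article, section {20c} on non-adherence and missing data. It opens with an expectation: "Secondary outcomes are unlikely to have missing data due to the nature of clinical follow-up". The reason offered is that "all patients are reviewed in person or by phone" while complications could still be observed.

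The rule itself begins "In the event that missing secondary outcomes are apparent". Analyses of the randomness of the missing data then serve "to determine whether complete case analysis is appropriate". The second branch reads: "In the event that the missing data does not conform to a random pattern, sensitivity analysis using worst-case, best-case scenarios" will be constructed and reported. No sensitivity analysis is planned for the branch in which the data look random. Multiple imputation in this section is tied to unreturned forms, that is, to the patient-reported outcome.

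The section on secondary outcome measures names floating toe as the most commonly reported complication and says how it is captured: "It will be recorded using a weight-bearing coronal view static photograph and manually rated". The secondary outcome analysis section specifies a logistic regression with odds ratios and adds no rule for missing data.

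**The concern.** Whether a patient's absence is related to the complication status that nobody recorded is not visible in the recorded data. A check built on recorded data can pass while loss is strongly outcome-related, and it will tend to pass when few patients are missing. The plan nevertheless uses the result of that check to decide whether the reader sees how far the missing patients could move the answer. In the likely case of few missing and no pattern found, the complication result would be a complete-case estimate with no planned bounds.

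The expectation of almost no missing data does not remove the concern. A phone review cannot supply a weight-bearing photograph, so a patient followed only by phone can count as reviewed and still lack the main component of the outcome.

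**Working it through.** The plan states a rule here, not a figure, so there is nothing to reproduce. The steps below test the rule.

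**1. What the check can see.** Let Y be complication status, X the observed data (arm, covariates, 3- and 6-month scores) and R=1 if Y is recorded. The data allow P(R=1|X) to be estimated, so dependence of loss on X can be found and missing completely at random rejected. Whether P(R=1|X,Y) also varies with Y needs Y for patients with R=0, which is what is missing. Outcome-related loss shows only as far as some X tracks Y.

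**2. A case where the check passes and the estimate is wrong.** Inputs: 123 procedures split 62/61 (sample size section, 1:1 allocation), a true rate of 60% in both arms, and 10% missing per arm (assumption).
- Flat-cut loses only non-events: 0.60/0.90 = 66.7%.
- Wedge-cut loses only events: 0.50/0.90 = 55.6%.
- Complete-case odds ratio: (0.556/0.444)/(0.667/0.333) = 0.63, against a true 1.00.

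In 4,000 simulated trials, Fisher's test of missingness by arm flagged 3.3% and a t-test of missingness on a baseline covariate flagged 4.8%. Under purely random loss the figures were 3.1% and 5.1%. One-sided rejection at 0.05 was 32.6% instead of 4.5%. This scenario is deliberately extreme. In a milder one, where only wedge-cut loses events and flat-cut loss is random, the odds ratio is 0.83, rejection is 12.4% and the flag rates are 2.9% and 5.1%.

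On power with few missing: Fisher's test with 40 per arm detects 15% v 5% missing about 18% of the time. That concerns loss by arm, not by outcome, and the plan names no test, so it is only an indication.

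**3. When the odds ratio is biased.** If events are lost with probability a and non-events with probability b in both arms, the odds in each arm are multiplied by (1−a)/(1−b), which cancels. With a = 1/6 and b = 0, 60% v 45% is observed as 0.50/0.90 = 55.6% v 0.375/0.925 = 40.5%. The odds ratio stays at 0.545, although both rates are wrong. If instead only flat-cut patients are lost by outcome (15% of events, 2.5% of non-events), flat-cut shows 0.51/(0.51+0.39) = 56.7% against 45%. A true 15-point difference then appears as 11.7.

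**4. What the bounds would show, by patient.** Assume 40 per arm, 4 missing in each, and 22/36 v 16/36 observed. The p-values are one-sided, from a pooled two-proportion z test.
- Complete case: 61.1% − 44.4% = 17 points, p=0.078.
- Worst for wedge-cut (its missing all events, flat-cut's none): 22/40 v 20/40 = 5 points, p=0.327.
- Best for wedge-cut: 26/40 v 16/40 = 25 points, p=0.013.

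**5. The same by procedure.** Here 62 v 61 procedures are used, with observed rates as near 60% and 45% as whole counts allow (the stated 15% reduction read as absolute). Risk differences are wedge-cut minus flat-cut.

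| Share missing (assumed) | Complete case | Best for wedge-cut | Worst for wedge-cut |
|---|---|---|---|
| 5% (3 per arm) | −0.145 | −0.187 | −0.089 |
| 10% (6 per arm) | −0.153 | −0.235 | −0.040 |
| 15% (9 per arm) | −0.161 | −0.284 | +0.008 |

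**The case against.** The best case for the plan has several parts.

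- **Few missing values are expected.** The 10% allowance belongs to the primary-outcome sample size, and none is stated for complications. This stands: 10% is an assumption here, and at 5% the bounds stay well on one side of zero. The expectation itself rests partly on phone review, which cannot yield the photograph. If photographs are also taken at earlier visits, some information would remain.
- **The odds ratio needs an unusual pattern to be biased.** Loss must depend on arm and outcome jointly, and participants and outcome assessors are blinded, which makes that less plausible. This stands and limits the size of the problem.
- **In the patient-level example the conclusion seldom changes.** The complete-case p is already above 0.05, and only the best case crosses it. This is correct. The example shows the width of the uncertainty, not a likely reversal.
- **The check is not defined, and 3- and 6-month scores might reveal outcome-related loss indirectly.** Both are true. No test or threshold is named, so the simulated flag rates belong to an illustrative check. A better check would still leave the dependence on Y unverified.

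A reader might also infer more than the documents support:

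- **That the rule contradicts the data integrity section**, which says "Patients who are otherwise lost to follow-up will be included in the analysis under an intention-to-treat framework". The same paragraph qualifies this ("Where appropriate, imputation will be used to provide estimates of outcomes for patients lost to follow-up") and foresees analyses using listwise deletion, so it already allows for complete-case work.
- **That sensitivity analysis is forbidden when the check passes.** The text only leaves it unplanned.
- **That multiple imputation must be the main handling.** Standard multiple imputation assumes missing at random and does not cure loss that depends on unseen complications. Choosing it would be a preference, not a consequence of this point.

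**Conclusion.** The point holds in a limited form. The plan makes best/worst-case reporting conditional on a check that cannot establish what it would need to establish, so passing it is no ground for leaving the bounds out.

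The size depends on how many complication outcomes are missing, which the documents do not state. The procedure-level bounds on the risk difference widen from −0.187 to −0.089 at 5% missing to −0.284 to +0.008 at 15%. Bias in the odds ratio further requires loss related to arm and outcome together. This concerns a secondary outcome and should be corrected, but it does not threaten the primary analysis.

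**What to change.** In section {20c}, remove the condition on the sensitivity analysis. State that best-case and worst-case results for complications will be reported alongside the main analysis whenever any complication outcome is missing, whatever the randomness check shows. State also the missing-data assumption under which the main analysis is valid. The randomness analyses can stay as description.

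The cost is a wording change, a few more tables and a wider reported range. No further patients or data are needed.
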